### Data analysis

Frequencies and percentages will be used to describe the population across key demographic and injury variables. We will compare the intervention and wait-list control groups across key variables (age at injury, injury severity, social risk, pre-injury behaviour, and pre-intervention behaviour) to detect any significant difference which may later compromise the generalisation of the findings.

Investigating the feasibility, clinical practicality, and acceptability of Signposts with videoconferencing support will be exploratory in nature. The objective is to collect information on ease of use, participant satisfaction, homework completion rates, programme completion and adherence, and attrition rates. Rates of programme attrition will be reported, as well as consumer satisfaction with the programme (reported as mean scores and percentages for items on the CSS).

To examine preliminary data on the impact of the programme on key outcome areas, we will compare the post-intervention scores on the CBCL scales, FAD, DASS, PS, and PSOC across the intervention and control groups and will report the mean and standard deviation of each group across these measures. To report preliminary findings on the maintenance of any treatment effects, means and standard deviations will be reported to assess any change within the intervention group from post-intervention to 4-month follow-up across the CBCL scales, FAD, DASS, PS, and PSOC. These findings may inform efficacy estimates for a larger RCT.

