### Parent outcomes when caring for a child post-TBI

Parental stress and family burden are also elevated following a child TBI. More specifically, behaviour disturbances post-TBI have been demonstrated to relate to higher parent distress and greater injury-related family burden [10]. Evidence suggests that this relationship is bi-directional, where parental distress, and mental health more generally, also uniquely predicts child behaviour problems [14]. Parents exhibiting greater distress are suggested to be less likely to adopt positive parenting styles to manage their child’s behaviour [15]. Relatedly, poorer parental communication [16] and disciplinary practices [17] relate to poorer post-TBI outcomes. Therefore, interventions which aim to reduce parent distress, and improve parental disciplinary styles and family functioning, may be particularly beneficial in improving post-paediatric TBI behaviour.

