## Methods/design

### Overall study design

The current pilot study employs a two-arm, parallel non-randomised design, in which a treatment as usual wait-list group is compared with a group in which the ‘Signposts’ programme is completed with clinician support via videoconferencing (see Fig. 1). The wait-list group may access any therapies or treatments considered standard treatment for a paediatric TBI.

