#### Parental functioning

Parental psychological distress will be measured using the Depression Anxiety Stress Scales (DASS) [46]. The DASS is a 42-item self-report inventory designed to measure the negative emotional states of depression, anxiety, and stress. Symptom levels on each subscale are categorised as falling in the normal, mild, moderate, severe, and extremely severe range according to the criteria outlined in Table 1.

**Table 1 Tab1:** Subscale severity criteria for the DASS

Severity	Depression	Anxiety	Stress
Normal	0–9	0–7	0–14
Mild	10–13	8–9	15–18
Moderate	14–20	10–14	19–25
Severe	21–27	15–19	26–33
Extremely severe	28+	20+	34+

Lovibond and Lovibond [46]

The total for each subscale will be used for analysis in the current study.

The Parenting Scale (PS) will be used to measure different styles of disciplinary practices [47]. The PS is a 30-item questionnaire that yields three measures of dysfunctional disciplinary styles in parents: laxness, overreactivity, and verbosity. A total dysfunctional disciplinary style score can be calculated where lower scores reflect better parenting. This score will be used for analysis in the current study.

The Parenting Sense of Competence Scale (PSOC) will be used to measure the parent’s self-reported competency and satisfaction in their parenting [48]. The scale consists of 16 items, from which two dimensions can be derived, reflecting satisfaction with their parenting role and sense of self-efficacy in the parenting role. Total scores across these two dimensions will be used for analysis, with higher scores reflecting greater satisfaction and efficacy.

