### Procedure

#### Recruitment

Eligible parents are identified by clinicians working in relevant departments at the Royal Children’s Hospital and the Victorian Paediatric Rehabilitation Service in Melbourne. Parents will then be allocated to either the intervention or wait-list control group on an alternating basis according to date of injury.

Recruitment letters will be mailed to parents, introducing the study and inviting them to participate. Parents are provided with information statements and sign the consent form should they wish to participate. Parents who do not accept or decline participation within 2 weeks will be followed up with a phone call.

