#### Data collection

Data will be recorded to capture the number of eligible parents approached, the number who consented to the programme, and the number who successfully completed the programme, as well as reasons for non-participation and non-completion.

Questionnaires will be administered using a secure online data collection instrument (RedCap), with parents sent web links at the appropriate time points. Upon enrolment in the study, parents will be sent the web-link questionnaires and asked to complete the outcome measure questionnaires retrospectively, reporting on their child and family’s functioning prior to the TBI. It is acknowledged that this may be vulnerable to parent reporting bias, particularly where children are several years post-injury. However, evidence suggests that post-TBI behavioural problems may not emerge or present for intervention until several years post-injury [10, 11], which means that including families several years post-injury more closely mirrors the clinical setting. It therefore seems reasonable to include such families in this feasibility study. Future research may aim to minimise this bias by reducing the eligible time since injury.

Prior to commencing the programme, approximately 1 month following initial questionnaire completion, parents will be asked to complete the measures again with regard to their family and child’s *current* functioning. Outcome questionnaires will again be sent in the form of web links via email immediately after the intervention and 4 months post-intervention. The approximate timeline for completion of these questionnaires is summarised in Table 2.

**Table 2 Tab2:** Summary of measures used

Construct	Measure	Time point			
		1	2	3	4
Socioeconomic status	Social Risk Index	●			
Outcome measures					
Child behavioural outcomes	Child Behavior Checklist	●	●	●	●
Family outcomes	McMaster Family Assessment Device	●	●	●	●
Parental functioning					
Parental psychological distress	Depression Anxiety Stress Scales	●	●	●	●
Confidence and satisfaction in the parenting role	Parenting Sense of Competence Scale	●	●	●	●
Disciplinary practices	Parenting Scale	●	●	●	●
Programme satisfaction	Consumer Satisfaction Scale			●^a^	

Time point 1 = retrospectively completed about pre-injury behaviour, 2 = pre-intervention, 3 = post-intervention, 4 = 4 months post-intervention

^a^Intervention group only

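### The comparability check of the two non-randomised arms lists no baseline of parental or family functioning (DASS, FAD, PS, PSOC), although these scores are collected before the programme and compared after it

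*Protocol article*

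**What the plan says.** Overall study design describes a "two-arm, parallel non-randomised design". Under Recruitment, eligible parents are identified, then allocated "on an alternating basis according to date of injury", and the text then turns to invitation letters and consent.

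Data analysis compares the arms on "age at injury, injury severity, social risk, pre-injury behaviour, and pre-intervention behaviour". The stated purpose is "to detect any significant difference which may later compromise the generalisation of the findings". The same section then compares post-intervention scores on the CBCL scales, FAD, DASS, PS and PSOC between arms, reporting means and standard deviations. It states no baseline adjustment.

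The baselines will exist. Data collection says: "Prior to commencing the programme, approximately 1 month following initial questionnaire completion, parents will be asked to complete the measures again". Table 2 marks the FAD, DASS, PS and PSOC at all four time points. Only the satisfaction scale is restricted to the intervention group.

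The Background section on parent outcomes says that "parental distress, and mental health more generally, also uniquely predicts child behaviour problems" and that "poorer parental communication [16] and disciplinary practices [17] relate to poorer post-TBI outcomes".

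**The concern.** Without randomisation, the comparability check is the main safeguard stated in the article for the between-arm contrasts. It covers injury, social status and child behaviour. It leaves out the parent and family scores, which matter in two ways.

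First, they are outcomes. The CBCL has its starting value on the list, but the DASS, FAD, PS and PSOC do not. For these four the plan states neither a baseline check nor an adjustment, so a difference present before the programme could be taken for a difference produced by it.

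Second, by the protocol's own account, distress and discipline are linked to the child's outcome. The caregiver also completes the CBCL, so parental state may affect both the behaviour and its rating.

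At stake are the efficacy estimates that Study aims and Data analysis intend to carry into a larger RCT.

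**Working it through.** **Listed baselines against compared outcomes** (Data analysis, Table 2)

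| Measure | Collected at time point 2 | In comparability list | Compared post-intervention |
|---|---|---|---|
| CBCL | yes | yes | yes |
| DASS | yes | no | yes |
| FAD | yes | no | yes |
| PS | yes | no | yes |
| PSOC | yes | no | yes |

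Neither remaining family of terms on the list fills the gap. Child behavioural outcomes ties behavioural functioning to the CBCL. Injury and demographic variables defines social risk as an aggregate of six aspects of social status.

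**Illustration of size.** The plan gives no figure to reproduce. The only input from it is 15 per arm (Sample size). Unit SD and chance-like allocation are assumed.

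- SE of a standardised baseline difference = sqrt(1/15 + 1/15) = 0.365 SD.
- P(|difference| > 0.5 SD) = 2 × (1 − Φ(0.5/0.365)) = 2 × (1 − Φ(1.37)) = 0.17. The same formula gives 0.41 for 0.3 SD and 0.03 for 0.8 SD.

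**Parent and family outcomes.** If baseline and post-intervention scores on a scale correlate at 0.3 to 0.7 (assumed), a 0.5 SD imbalance carries 0.3 × 0.5 = 0.15 SD to 0.7 × 0.5 = 0.35 SD into the unadjusted contrast on that scale.

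**CBCL.** Assume that distress correlates at r = 0.3 to 0.5 with the CBCL, and take the T-score SD of 10.

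- Unadjusted contrast: r × 0.5 × 10 = 1.5 to 2.5 T points.
- Adjusted for baseline CBCL: assume r is the same before and after the programme, and that the CBCL correlates with itself over time at b = 0.3 to 0.7. The expected remainder is r × (1 − b) × 0.5 × 10. The lowest value is 0.3 × 0.3 × 5 = 0.45 and the highest is 0.5 × 0.7 × 5 = 1.75 T points.

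**Would a significance test find it?** If the comparison is by a two-sided 5% test with 15 per arm, power for a true 0.5 SD difference is Φ(1.37 − 1.96) = 0.28 (0.26 by the t distribution). Power of 80% needs (1.96 + 0.84) × 0.365 = 1.02 SD. Adding the scores to the list would therefore help little if they were only tested.

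**The case against.** **The list may not be exhaustive.** The article calls these key variables and does not say that other baselines will go unreported. A full protocol or SAP, not shown, may carry more rows. That is fair, and a reader should not infer that the omitted baselines will be withheld. But the article prints a specific list, and that list omits variables its own Background calls predictive. The point rests on that stated choice.

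**Some family and parent information is covered.** Social risk is a family-level baseline, so it would be wrong to say that no parent or family characteristic is checked. Participants also excludes diagnosed severe psychiatric disorder in the parent, which narrows the range of parental mental health. Neither measures distress, discipline, competence or family functioning among those enrolled.

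**The CBCL is partly protected.** If distress affects the child's behaviour or the parent's ratings, it should already show in the pre-intervention CBCL, which is listed. This stands: only the residual path escapes. A reader might take 1.5 to 2.5 T points as the bias in the main clinical measure. That figure is for the unadjusted contrast under assumed correlations.

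**The figures describe chance, not confounding.** This also stands. Chance imbalance is already part of the sampling error: at SD 10 the unadjusted CBCL contrast has an SE of 10 × 0.365 = 3.65 T points, so 1.5 to 2.5 is about 0.4 to 0.7 of one SE. Scanning six scores (FAD, three DASS subscales, PS, PSOC) for at least one gap above 0.5 SD gives 45% to 63% by simulation, at assumed correlations of 0.7 to 0.3. Any six such variables would do the same, so nothing is built on it here.

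**No systematic mechanism.** Alternation by date of injury does not in itself sort families by distress. However, allocation is described before invitation and consent. If invited parents know their arm, willingness to join could depend on distress or perceived competence. The article does not say whether they know, so systematic imbalance is possible but not shown.

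**Conclusion.** The concern holds in a limited form. The stated check contains no baseline of parental or family functioning, while these scores are collected in both arms at time point 2 and compared afterwards without a stated adjustment. An imbalance would go undetected by that check and could be read as a programme effect, mainly on the DASS, FAD, PS and PSOC and only residually on the CBCL.

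The 17% figure is illustrative and assumes chance-like allocation. The 0.15 to 0.35 SD and T-point ranges rest on assumed correlations. The documents do not support the inference that the arms will in fact differ on distress, or that the CBCL contrast is biased by a known amount.

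Severity is minor to moderate. The primary aim is feasibility and acceptability, the outcome contrasts are preliminary, and no confirmatory decision depends on them. They are nevertheless meant to inform efficacy estimates for a larger RCT.

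**What to change.** In Data analysis, extend the list with: *and pre-intervention DASS subscales, FAD-GF, PS total and PSOC*. Report these as group means, SDs and standardised differences instead of significance tests. State that each post-intervention parent and family contrast will be read against its own time point 2 score.

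Optionally, add one exploratory sensitivity estimate of the CBCL difference that also adjusts for a single prespecified DASS score. Parental functioning uses three DASS subscale totals, so the choice must be fixed in advance. With 30 families the estimate will be imprecise, and the main fix does not depend on it.

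The cost is a few more rows in the baseline table and a sentence of text, plus one small model if the option is taken up. No further data collection is needed.

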### Participants

Participants are the primary caregivers (herein referred to as parents) of at least one child who has sustained a TBI within the prior 2 years. Children aged 2.0–6.11 at the time of injury, who sustained mild, moderate, or severe injuries, will be eligible to participate.

Inclusion criteria for the current study are that medical records suggest that parents and children have sufficient English skills, that the child has no prior history of neurological or developmental disorder, no diagnosed severe psychiatric disorder in the parent, and no documented evidence that the TBI was non-accidental.

In keeping with previous research [38], TBI will be classified by injury severity (mild, moderate, or severe). For young children, these categories are largely based on scores on the Paediatric Glasgow Coma Scale (GCS) [39], which provides ratings of the depth and/or duration of altered consciousness post-injury. As an adaptation to the initial scale devised for use in adults [40], GCS is instead rated in young children by recording behavioural rather than verbal responses. Scores are assigned on a scale of 3–15, where 3 indicates no verbal, motor, or visual responsiveness to stimuli, and 15 indicates full responsiveness.

Classifications of injury severity are made according to the following criteria:(i)Mild: GCS 13–15, no evidence of mass lesion on CT/MRI and no neurological deficits(ii)Moderate: GCS 9–12, mass lesion or other evidence of specific injury on CT/MRI and/or neurological impairment(iii)Severe: GCS 3–8, mass lesion or other evidence of specific injury on CT/MRI and/or neurological impairment

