#### Intervention procedure

Prior to commencement of this study, the Signposts clinician will complete the Professional Training Workshop through the Parenting Research Centre in Melbourne, where the original Signposts programme was developed. Workbooks and modules used in the current study are in the original hard copy form, available through the Parenting Research Centre. In addition, this project uses the stand-alone adjunct module ‘Dealing with a head injury in the family’, developed by Woods and colleagues [20].

Children must be at least 3 months post-injury before their parents commence the programme. When ready to commence the programme, participants engage in an initial face-to-face interview with the Signposts clinician, which provides the opportunity to build rapport and further explain the requirements of the programme, including demonstration of the iPads and the videoconferencing software. Initial modules required to begin the programme (1–3, 8, and 9) are provided at this session. The programme is commenced after this initial interview.

Parents work through module booklets in their own time and complete the relevant tasks in their workbook. On five occasions, approximately 2 weeks apart, parents engage in a one-on-one videoconference session with the Signposts clinician. The session follows the suggested structure for telephone support from the practitioner manual, which generally aims to support parents in completing homework and answer any questions or concerns that may arise.

In line with previous research [21], some programme modules were grouped together for logistical purposes. The approximate timeline for the completion of modules and videoconference sessions is presented in Table 3. Aside from the initial modules provided at the pre-intervention interview, subsequent modules (4–7) are individually sent to the family via post, as needed.

**Table 3 Tab3:** Programme for completion of Signposts programme with online clinician support

Week	Parent homework	Clinician contact
0		Pre-intervention interview
1	Read modules 1–3, 8, and 9 Begin homework	
2	Complete homework for modules 1–3, 8, and 9 prior to videoconference	Videoconference #1 Homework reviewed for modules 1–3, 8, and 9
3	Read module 4 Begin homework	
4	Complete homework for module 4 prior to videoconference	Videoconference #2 Homework reviewed for module 4
5	Read module 5 Begin homework	

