### Sample size

The current feasibility study sample will aim to consist of 15 parents who will participate in the intervention and a further 15 allocated to the wait-list control group. Studies also exploring the feasibility of family-centred behaviour interventions in this population used similar sample sizes [49–52] and detected promising preliminary results. With recruitment in this population frequently difficult and slow, we aim to measure the duration of time taken to recruit this sample in order to guide estimates of recruitment duration for a larger RCT.

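### A search for significant baseline differences with 15 per arm cannot show that the non-randomised groups are comparable; imbalances below about 1 SD could go unflagged and enter the outcome comparison

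*Protocol article*

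**What the plan says.** Under Overall study design, the article states: "The current pilot study employs a two-arm, parallel non-randomised design". The Sample size section aims for "15 parents who will participate in the intervention and a further 15 allocated to the wait-list control group". The Recruitment section gives the allocation rule: "Parents will then be allocated to either the intervention or wait-list control group on an alternating basis according to date of injury". Invitation letters and consent come after that step.

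The Data analysis section then compares the groups on "age at injury, injury severity, social risk, pre-injury behaviour, and pre-intervention behaviour". The stated purpose is "to detect any significant difference which may later compromise the generalisation of the findings". The list is closed, and time since injury is not on it. No other criterion for judging comparability is given.

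For outcomes, the same section compares post-intervention scores between groups on the CBCL scales, FAD, DASS, PS and PSOC and reports means and standard deviations. It says the findings may inform efficacy estimates for a larger RCT. All five instruments are also completed at time point 2, before the intervention (Table 2).

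**The concern.** In a non-randomised study, the baseline comparison has to show how far apart the groups are. A significance test answers a different question, and with 15 per arm its answer is dominated by sample size. A sizeable gap can return a non-significant result.

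The outcome comparison, as described, uses post-intervention scores alone. Part of any baseline gap would then appear as a group difference that the programme did not cause, or would mask one that it did. The estimates meant to guide the larger RCT would inherit that error.

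The threat is also misnamed. A difference between arms biases the contrast between them, which is a matter of internal validity. Generalisation concerns whether the results apply to other families.

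Time since injury is a natural variable to compare. Parents qualify if they have "at least one child who has sustained a TBI within the prior 2 years". The Background says behaviour changes grow over time, and the Data collection section links a longer interval to biased recall of pre-injury functioning and to late emergence of problems.

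**Working it through.** The article gives no power, significance level or effect size for 15 per arm; it justifies the number by similar feasibility studies. There is no figure of the plan's own to reproduce.

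**Inputs**
- n = 15 per arm (Sample size).
- CBCL T-score SD = 10 (Child behavioural outcomes). This is the scale norm, not an estimate for this sample.
- Two-sided 5% level: assumed.
- True imbalance d of 0.3 to 1.2 SD: assumed range.

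**Smallest observed gap that is significant**
- Standard error of a standardised difference: √(2/15) = 0.365.
- Critical t on 28 degrees of freedom: 2.048.
- 2.048 × 0.365 = 0.75 SD, about 7.5 T points.

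**Power for a true imbalance d** (two-sample t-test, non-centrality d/0.365; normal approximation Φ(d/0.365 − 1.96) alongside)

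| True imbalance | t-test | Normal approx. |
|---|---|---|
| 0.3 SD | 12.5% | 12.7% |
| 0.5 SD | 26% | 28% |
| 0.8 SD | 56% | 59% |
| 1.0 SD | 75% | 78% |
| 1.2 SD | 89% | 91% |

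A true 0.5 SD imbalance is thus missed about 74% of the time, and 0.8 SD about 44%.

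**Imbalance detectable with 80% power**
- Normal approximation: (1.960 + 0.842) × 0.365 = 1.02 SD.
- t-test: 1.06 SD, about 10.6 T points.
- To reach 80% power at 0.5 SD would take about 64 per arm by t-test, so the screen cannot be repaired at this sample size.

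**Categorical variables.** The t-test does not apply to injury severity, or to social risk if it is used as low versus high. For a binary variable, Fisher's exact test has 11% power for 20% v 40%, 23% for 30% v 60% and 45% for 20% v 60%. An observed split of 3/15 v 9/15 gives p = 0.060 and would not be flagged.

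**Carry-over into the outcome.** With an assumed pre/post correlation of 0.6 to 0.8 and equal SDs, a 0.5 SD (5-point) gap at time point 2 shifts the unadjusted post-intervention difference by 0.6 × 5 = 3 to 0.8 × 5 = 4 T points with no treatment effect.

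**Time since injury under the allocation rule.** Assume it is uniform over 3 to 24 months, so its SD is 21/√12 = 6.1 months. Strict alternation of 30 families in date order leaves an expected gap between arms of 21/31 = 0.7 months. If half of 60 allocated families consent, unrelated to arm, simulation gives an SD of about 1.6 months for that gap. Alternation therefore tends to balance this variable. Only consent, start time or dropout that differs by arm could produce a large gap.

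**The case against.** The primary aim is feasibility and acceptability; retention, adherence, recruitment time and satisfaction do not depend on baseline balance. The outcome comparison is called preliminary. Pre-injury and pre-intervention behaviour, probably the most important covariates, are already on the list. Covariate adjustment is commonly left to an analysis plan, which is not shown, so its absence from an article is not itself an error. All of this stands and limits the weight of the point. It does not rescue the significance criterion, which the article states outright.

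A reader might infer more than the text supports:

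- *That non-significance will be declared to be balance.* The article never says so. It only gives no other criterion.
- *That 15 per arm cannot detect imbalance at all.* Gaps above about 1 SD usually would be detected.
- *That leaving out time since injury hides serious confounding.* Alternation by injury date works against this. The omission is a reporting gap, which matters because allocation precedes consent.
- *That wait-list families will be assessed sooner after injury.* The Intervention procedure section says "Children must be at least 3 months post-injury before their parents commence the programme" and names only programme start, but Overall study design promises control data at equivalent time points. How the two fit together is unclear; an earlier wait-list assessment is not established.
- *That the screen has a 23% chance of a false flag* (1 − 0.95⁵ = 0.226). This needs five independent tests. The CBCL has three summary scores and is used at both behavioural time points, so neither the number of tests nor their independence is settled.

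**Conclusion.** The point holds, at moderate weight. The only stated comparability check in this non-randomised 15 v 15 comparison is a search for significant differences. At an assumed two-sided 5% level it would miss most true imbalances of 0.5 SD and nearly half of those of 0.8 SD. Imbalances below about 1 SD could go unflagged and carry into the post-intervention comparison. The T-point figures rest on the scale SD of 10, and the 3 to 4 point carry-over on an assumed correlation. The article also names the wrong consequence: imbalance affects the validity of the comparison. Feasibility and acceptability results are unaffected.

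**What to change.** 1. In Data analysis, replace the search for significant differences with group means and SDs, or counts, together with standardised differences and 95% intervals, without p-values. Near zero difference, these intervals will be about ±0.75 SD wide, which shows plainly how little can be concluded about balance.
2. Estimate each post-intervention group difference adjusted for the time point 2 score of the same measure, whatever any baseline comparison shows. If the full analysis plan already specifies this, say so in this section. The adjustment addresses imbalance in the measured score, not in unmeasured factors.
3. Add time since injury to the variables compared. It can be derived from the injury date used for allocation.
4. Name comparability of the groups, rather than generalisation, as what a baseline difference may compromise.
5. Reconcile Overall study design with Intervention procedure on when wait-list assessments take place relative to injury. No particular minimum is proposed here.

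The cost is a few sentences, slight extra analysis and one degree of freedom per adjusted model (residual 28 becomes 27 with 30 families). No new data are needed, and the efficacy comparison remains preliminary.

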### Study aims

The primary aim of the current study is to investigate the feasibility and acceptability of conducting Signposts with videoconferencing as the mode of clinician support. In particular, this study intends to investigate this in families where the child sustained the TBI in early childhood, an age group that may be particularly prone to post-TBI poor outcomes [35–37] but, to date, has been relatively neglected with minimal attention directed to development of age-appropriate evidence-based interventions targeting behaviour problems.

More specifically, the study objectives are to:Investigate the feasibility of delivering the programme with clinician support via videoconferencing, with the goal of developing a larger RCT. This will be investigated with the collection of data on sample retention rates, participant programme adherence, and duration to reach target sample size.Collect information to inform on the clinical practicality of delivery through this medium, including the duration of videoconference sessions, rate of technology difficulties that cause disruption to sessions, and the time frame for programme completion (in weeks).Explore the acceptability of the programme when delivered through this medium, with completion of a consumer satisfaction survey, as well as by enquiring on the participant’s comfort with using the technology. It is expected that, consistent with programme delivery through different modalities, the programme will have a high level of consumer satisfaction in this population when delivered with clinician support via videoconferencing.Explore preliminary clinical outcomes across those who completed the programme compared with those on a wait-list, in order to inform likely efficacy estimates for a fully powered RCT. Primary measures will assess child behaviour, while secondary outcome measures will assess parent distress, parenting disciplinary style, parenting sense of competency, and family functioning. These will be measured using questionnaires considered standard for research involving the Signposts programme (see, for example, Woods and colleagues [23]). It is expected that those who complete Signposts will report reductions in post-TBI child behaviour problems, parental distress, and dysfunctional parenting, while increasing family functioning and parental sense of competency.

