**Fig. 1 Fig1:**
[figure not shown]
Participant flow diagram

Data will be collected at four time points: (i) pre-injury functioning at the time of enrolment in the study and then (ii) pre-intervention, (iii) immediately post-intervention, and (iv) at the 4-month follow-up post-intervention. Data collected from those who complete the intervention will be compared with data collected at equivalent time points from a wait-list control group. This study has been granted ethics approval by the Human Research Ethics Committee of the Royal Children’s Hospital, Melbourne.

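### The preliminary efficacy comparison uses post-intervention scores alone, although two non-randomised groups of 15 both supply pre-intervention scores on every outcome

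*Protocol article*

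**What the plan says.** Data analysis in the protocol article gives the between-group efficacy comparison: "we will compare the post-intervention scores on the CBCL scales, FAD, DASS, PS, and PSOC across the intervention and control groups". The results promised are the mean and standard deviation of each group. No change score, covariate or other adjustment is named.

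The pre-intervention scores exist. Overall study design states that "Data will be collected at four time points", and that data from the intervention group "will be compared with data collected at equivalent time points from a wait-list control group". Data collection adds that before the programme starts "parents will be asked to complete the measures again with regard to their family and child’s" current functioning. Table 2 marks CBCL, FAD, DASS, PSOC and PS at all four time points and restricts only the satisfaction scale to the intervention group.

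The design is a "two-arm, parallel non-randomised design", and parents are "allocated to either the intervention or wait-list control group on an alternating basis according to date of injury". Sample size sets 15 per group.

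Pre-intervention data have one stated use. Data analysis will compare the groups on age at injury, injury severity, social risk, and behaviour before the injury and before the intervention, looking for a significant difference that might limit generalisation. Nothing is said to follow from that check for the effect estimate.

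**The concern.** The expected effect is worded as change: "It is expected that those who complete Signposts will report reductions in post-TBI child behaviour problems". A comparison of post-intervention means does not measure change. It also leaves any pre-intervention difference between the groups inside the estimate. Groups of 15 can differ by several T points by chance alone, and because allocation is not random, systematic differences cannot be excluded either.

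Two things are at stake. The estimated group difference may be displaced by where the groups started, and it is less precise than the collected data allow. Study aims and Data analysis both say that the clinical results are to inform efficacy estimates for a larger RCT, so the weakness could carry into the planning of that trial.

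**Working it through.** The article gives no target difference, alpha or power, so there is no figure of its own to reproduce. The check sizes the consequence.

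**Inputs from the article:** n = 15 per group (Sample size); SD = 10, the CBCL T-score norm (Child behavioural outcomes).

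**Assumed:** the sample SD equals the norm; pre-post correlation r = 0.5 to 0.8; an illustrative baseline gap of 5 T points; two-sided 5% level for the baseline check.

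**1. Chance baseline gap.** SE of a group difference = SD × √(2/n) = 10 × √(2/15) = 3.65. Probability of a chance gap above 5 points = 2 × [1 − Φ(5/3.65)] = 0.17.

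**2. What the planned check can see.** With t(28) = 2.048, an observed gap must reach 2.048 × 3.65 = 7.5 points to be significant. For a true gap of 5 points the noncentrality is 5/3.65 = 1.37, and power from the noncentral t with 28 df is 26%. The check covers behaviour only, so a gap on FAD, DASS, PS or PSOC would not be looked for.

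**3. Carry-over of a 5-point gap into the post-only difference.**
- *Chance gap* (scores regress to a common mean, equal SDs): shift = r × 5 = 2.5, 3.5 and 4.0 points at r = 0.5, 0.7 and 0.8. A simulation of 40,000 studies per r with no treatment effect gave post-only means of 2.49, 3.52 and 4.01, and baseline-adjusted means of −0.01, 0.02 and 0.01.
- *Stable group difference:* the full 5 points stay in the post-only difference. Adjustment leaves (1 − r) × 5 = 2.5, 1.5 and 1.0 points.

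**4. Precision with no systematic gap.** Post-only half-width = 2.048 × 3.65 = 7.5. Adjusted half-width = 2.052 × 3.65 × √(1 − r²), with t on 27 df:

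| r | Adjusted half-width | With factor √(1 + 1/26) on the SE | Equivalent unadjusted n per group, 15/(1 − r²) |
|---|---|---|---|
| 0.5 | 6.5 | 6.6 | 20 |
| 0.7 | 5.4 | 5.5 | 29 |
| 0.8 | 4.5 | 4.6 | 42 |

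At a correlation as low as 0.3 the corrected SE is 3.55 against 3.65, so adjustment gains little there but does not lose precision.

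**The case against.** The strongest case against has four parts.

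**The study is about feasibility.** Clinical outcomes are the fourth objective and are called preliminary. This stands, and it limits how serious the point is. A reader might go further and quote the power lost by not adjusting. The article states no efficacy test or target difference, so such a figure would describe a test the plan does not contain.

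**The wording may leave room for adjustment.** An ANCOVA also compares post-intervention scores, and an article may leave the model to a fuller document. This reading is strained, because the only summaries promised are each group's mean and SD and no adjusted difference is mentioned.

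**Baseline is not ignored.** Pre-intervention behaviour, the primary clinical measure, is compared between groups. That is correct, and it would be wrong to say that the plan makes no use of pre-intervention data. The check is nevertheless weak, omits four of the five instruments and changes nothing in the estimate.

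**The size of the bias is easily overstated.** A reader might infer that any imbalance passes whole into the result. That holds only for a stable group difference; a chance gap carries over in proportion to r, and chance imbalance is already part of the 3.65 SE. Nor do the documents show that alternation by date of injury favours either arm. The 17% in step 1 is a chance figure and cannot support a claim of systematic imbalance.

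**Conclusion.** The point holds as a should-fix on an exploratory objective. The stated between-group comparison makes no use of the pre-intervention scores that both groups provide on every outcome, and the planned baseline check does not make up for this. On the CBCL, a 5-point gap would shift the estimate by 2.5 to 4.0 points if due to chance, and by up to the full 5 if stable. The 95% half-width is 7.5 points where about 4.5 to 6.5 is attainable.

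These sizes rest on the normative SD of 10, on r between 0.5 and 0.8, and on an illustrative gap; the documents supply only the SD. FAD, DASS, PS and PSOC are affected in the same way but cannot be sized from the article.

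A reader might also infer that adjustment would put the two arms on the footing of a randomised comparison. It would not: the near-zero adjusted result in step 3 depends on the gap being a chance one, and unmeasured differences between the groups would remain. The feasibility, practicality and acceptability results are untouched.

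**What to change.** In Data analysis, replace the post-score comparison with an ANCOVA for each outcome: regress the time-point-3 score on group and on the same measure's time-point-2 score. Report the adjusted mean difference with its 95% CI, beside the raw means and SDs of both groups at both time points. Add a sentence saying that this adjustment does not remove all confounding from non-random allocation, so that those planning the larger RCT read the estimate accordingly.

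The cost is wording and one degree of freedom per model. No new data, visits or participants are needed.
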